### Endpoint Definitions and Hypothesis

The primary endpoint of the study will be a device oriented complex endpoint (DOCE). A complex endpoint has been defined, to assess hemostasis devices from both important clinical viewpoints: its efficacy in containing puncture site bleeding and its safety in terms of preserving radial artery patency and integrity.

DOCE will encompass the following: post-operative bleeding with visible hematoma formation after hemostasis device removal classified using the EASY methodology (17) (I), RAD, encompassing vessel dissection, (pseudo)aneurism and/or fistula formation (II) and RAO (III). These three parameters will be measured and quantified first at 24 hours after hemostasis device removal or at hospital discharge (whichever comes sooner), and again assessed at the 60-day follow-up visit.

Secondary endpoints will focus on human resource requirements and economics of devices. These include initial compression to achieve primary hemostasis (I), overall compression device usage time (II), and number of compression devices needed (III). Primary hemostasis is defined as the time in minutes, from application of the hemostasis device to the first successful decrease of the initial torniquet pressure, with success indicating no repeat bleeding from the puncture site. Overall compression time refers to total time of devices used as a hemostasis tool. In cases of acute bleeding following device use, a new, freshly opened tool may sometimes be required if the first one failed to contain bleeding. According to the RAPHE protocol, in case of initial device failure, a second, identical tool is to be utilized. If the second device also fails to contain puncture site bleeding, a bail-out hemostatic device will be employed. Thus, our last tertiary endpoint has been defined as follows: the need for a bailout compression method (I).

We hypothesize, that utilizing either of the novel bioactive devices in a standalone arrangement will prove clinically non-inferior to the other study and the control MCD, respectively. Furthermore, we assume, that the use of either one of the standalone bioactive devices will require less compression time, fewer human resources, and less management to successfully handle as compared to the MCD.

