### Sample Size Calculation

Sample size calculation was carried out for non-inferiority studies following established guidelines (18, 19) with a significance level of 95% and a power of 80%. Although the best reported component of the DOCE, RAO rates range from < 1 to 33% (4), and it would be advisable to estimate sample size calculations for the worst-case scenario (i.e., 33%), however analyses of our own existing data regarding RAO and RAD (The RadPress trial—unpublished) deemed this value unreasonable for the centers involved. Therefore, we used a conservative 15% of the population rate for the DOCE for both intervention and control treatments. We allowed a 10% relative inferiority margin for the investigated treatments (20). The resulting sample size was 158 patients per arm. We also accounted for a potential 10% drop-out rate and factored in the uncertainty in true DOCE rates, and hence sample size estimates, and thus rounded the sample size to 200 patients per arm.

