### Statistical Analyses

Data analysis will be done on an intention to treat basis. Baseline patient and disease characteristics will be summarized with detailed descriptive statistics that entail mean, median, SE, SD, IQR and range for continuous variables, while for categorical variables absolute and relative frequencies will be reported. Hypothesis testing of the primary outcome will be done with Fisher’s exact test with a significance level of 95%. Univariate analyses of secondary endpoints will be carried out as superiority analyses with one-way ANOVA, Kruskal-Wallis test, or logistic regressions, depending on the outcome variable type and distribution. Multivariate analyses of secondary endpoints will entail using general or generalized hierarchical mixed effects models depending on variable type and distribution. All statistical analyses will be done in the R statistical environment (21).

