RAPHE will focus on RAO, RAD and bleeding equally, from a device-oriented endpoint as all present clinical challenges influence quality of life of patients. With RAO, a conduit for further use is eliminated and clinical signs of upper extremity ischemia may present, necessitating surgical or endovascular treatments. Damage to the radial artery, clinically mostly manifesting as (pseudo)aneurysm and fistula formation can cause substantial pain/discomfort, paresthesia and even a palpable mass above the site of the puncture often causing a thrill in case of an arterio-venous fistula. These pathologies will likely require interventional methods or surgical repair to avoid chronic vascular conditions (5–8) and may cause a notable decrease in quality of life if left unchecked and/or untreated. Bleeding as the most common complication after TRA if serious may present as a significant or even critical issue. Thus a “perfect” compression device has a DOCE of zero per cent, as it causes no bleeding, RAO or RAD. In the RAPHE study we expect an overall DOCE rate, encompassing everything above of around 15% in all three arms of the trial.

The main goal of the study will be to determine, how standalone bioactive chitosan and/or potassium ferrate devices fare against the gold standard pneumatic airbladder based MCD. Besides clinically relevant safety and efficacy profiles, we will opt to also explore if fewer human resources are required to manage said bioactive devices. As per the RAPHE protocol, bioactive devices only require one adjustment, shortly after application and may require less overall compression time. Reducing the need for extensive human resource PH management and continuous MCD adjustments in high-volume centers is favorable, due to a multitude of factors. As bioactive devices do not require adjustments every 10–20 min, additional staff, managing strict PH protocols may be allocated elsewhere. In the RAPHE study we assume that patients randomized into one of the two investigational arms (potassium ferrate disc or chitosan sponge) will achieve primary hemostasis quicker and require less overall compression time as compared to MCD control subjects. From an economic point of view, the RAPHE trial will also be assessing the need of hemostasis units per patient in all three arms, and record if bail-out compression devices are needed. We have no convincing assumptions regarding these endpoints, due to a lack of prior reported data or in-house registries.

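### The primary hypothesis mixes device-versus-device with device-versus-MCD non-inferiority, at odds with the stated main goal, and the 80% power covers only one contrast

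*Protocol article*

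**What the plan says.** The primary endpoint is the device-oriented composite (DOCE) of hematoma, radial artery damage and radial artery occlusion. Under Endpoint Definitions and Hypothesis, the article expects that "utilizing either of the novel bioactive devices in a standalone arrangement will prove clinically non-inferior to the other study and the control MCD, respectively". Written out, that is four directed claims: chitosan against the MCD, potassium-ferrate against the MCD, chitosan against potassium-ferrate, and the reverse.

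Other sections use a narrower comparison:

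- Discussion: "The main goal of the study will be to determine, how standalone bioactive chitosan and/or potassium ferrate devices fare against the gold standard pneumatic airbladder"-based MCD.
- Safety and Termination: the interim analysis asks whether a novel option is better or worse than the MCD.
- Sample Size Calculation: "we used a conservative 15% of the population rate for the DOCE for both intervention and control treatments". It adds "We allowed a 10% relative inferiority margin for the investigated treatments", and then "The resulting sample size was 158 patients per arm". Level and power are given once: "with a significance level of 95% and a power of 80" per cent.
- Statistical Analyses: "Hypothesis testing of the primary outcome will be done with Fisher’s exact test with a significance level of 95" per cent. No contrast is named.

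**The concern.** The hypothesis section and the rest of the article do not describe the same confirmatory question. The hypothesis gives the other investigational device the same standing as the established control. The Discussion, the interim comparison and the sizing all use the MCD as the reference. The words *either* in the hypothesis and *and/or* in the Discussion also leave open whether the trial succeeds when one device passes or only when both do.

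Two things are at stake. First, the article itself says that adequately powered studies of standalone use are lacking, so non-inferiority to the other study device is non-inferiority to an unproven comparator. It says nothing about whether the MCD can be replaced, yet it could be reported as a success if read as a claim of its own. Second, a reader may take the 80% power to cover the whole hypothesis, when it covers one pairwise comparison.

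**Working it through.** **Inputs from the article.** DOCE 15% in intervention and control; margin 10%; level 95% (read as alpha 0.05, sidedness not stated); power 80%; 158 per arm before inflation; 10% drop-out; 200 per arm enrolled, so 200 × 0.9 = 180 evaluable.

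**Step 1: reproduce 158.** For two equal rates p and an absolute margin d,

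n = (z_alpha + z_beta)² × 2p(1 − p) / d² = (1.645 + 0.842)² × 2 × 0.15 × 0.85 / 0.10² = 157.7, so 158.

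This matches exactly with a 10-point absolute margin and one-sided 5%. One-sided 2.5% would give 201. A margin that is 10% of 15% (1.5 points) would give 7,007 at one-sided 5%. So 158 is one contrast at an undivided one-sided 5%. The steps below use that reading. That the margin is called relative is a separate matter.

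**Step 2: what a device-versus-device pass means.** Assume an unpooled Wald test against the 10-point margin. (The Fisher test as stated carries no margin, so this is an assumed analysis.) The device with the lower observed rate has a difference of zero or less, so its statistic is at least 0.10/SE. The SE is largest when both rates are 50%:

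- 180 per arm: SE = √(2 × 0.25/180) = 0.0527; 0.10/0.0527 = 1.90 > 1.645.
- 158 per arm: SE = √(2 × 0.25/158) = 0.0562; 0.10/0.0562 = 1.78 > 1.645.

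At one-sided 5%, one direction therefore passes whatever the data are. At one-sided 2.5% (critical value 1.96) this is not guaranteed at 158 or 180. With both devices at 30%, simulation still gives 97% at 158 and 99.99% at 180.

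**Step 3: both devices at the margin (25%, MCD 15%).** In 500,000 simulated three-arm trials with 180 per arm at one-sided 5%:

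- A given device passes against the MCD in 5.1%, and at least one device in 9.3%. At one-sided 2.5% the latter is 4.8% to 4.9%.
- Neither device passes against the MCD in 90.7%. In all of those trials, one device-versus-device direction is met; both directions are met in 44% of them.
- If a device must pass against both the other device and the MCD, some device succeeds in 9.3%, the same as for the MCD contrasts alone. Under that conjunction the extra contrast adds no type I error.

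**Step 4: power with all arms at 15%, one-sided 5%.**

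| Success means | 158 per arm | 180 per arm |
|---|---|---|
| One named contrast | 80% | 84% |
| At least one device vs MCD | 93% | 95% |
| Both devices vs MCD | 68% | 74% |
| All four directed claims | 48% | 57% |

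The third row follows from the first two: at 180, 2 × 0.8445 − 0.9501 = 0.739; at 158, 2 × 0.8025 − 0.9273 = 0.678.

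**The case against.** The strongest defence is that the article does point to a deciding comparison. The MCD is called the control, the Discussion names it in the main goal, the interim analysis uses it, and the sizing speaks of intervention and control. One loosely worded sentence mentions the other study device, and nowhere is a device-versus-device result alone said to count as success. This stands in part: a reader might infer that no contrast is decisive, and the documents do not support that. What remains is that the hypothesis sentence, the formal statement of what is to be shown, disagrees with those sections.

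A reader might also infer that the hypothesis is partly met even when both devices fail against the MCD. That requires splitting the sentence into free-standing claims. The text joins them with *and*; read as a conjunction, a device that fails against the MCD fails the hypothesis. The wording does not settle which reading is meant. Nor is the 90.7% in the working an error rate: two devices with equal true rates are truly non-inferior to each other, so the claim is correct but uninformative.

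Finally, a reader might infer that each contrast is tested at full alpha. The article gives one level and assigns it to no contrast, and a multiplicity rule may sit in an analysis plan that is not shown, so its absence is no finding. It is also defensible to test two distinct products against a shared control each at the full level when claims are made per device, and power per contrast is the usual convention. These points stand. For that reason joint control is recommended below only conditionally.

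**Conclusion.** The point holds as a conflict within the protocol article. The primary hypothesis includes device-versus-device non-inferiority and leaves open whether one or both devices must succeed, while the stated goal, the interim comparison and the sample size concern devices against the MCD. The device-versus-device claim cannot support replacing the MCD, and at one-sided 5% one direction of it is always met. The 80% describes one contrast; requiring both devices against the MCD gives 74% at 180 evaluable (68% at 158), and all four claims 57% (48%).

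The figures rest on a 10-point absolute margin, one-sided 5%, an unpooled Wald test and, for power, a true DOCE rate of 15% in every arm. The false-claim figure of about 9% supposes both devices truly at 25% and applies only if at least one device passing is the success criterion. The matter should be corrected, but it does not by itself invalidate the design.

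**What to change.** - **Endpoint Definitions and Hypothesis:** name chitosan versus MCD and potassium-ferrate versus MCD as the two primary non-inferiority contrasts on DOCE, with a separate claim per device. Report device versus device only as a descriptive risk difference with its confidence interval.
- **Sample Size Calculation:** state that the 80% power is per device-versus-MCD contrast.
- **Only if a claim that at least one device is non-inferior is intended:** control the two MCD contrasts together, for example by Holm's procedure, which brings the 9.3% above down to about 4.9%.

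The first two changes are wording only and need no extra patients. They should be settled before comparative data are reviewed, including at the interim analysis. Holm has a cost: with 180 evaluable, per-device power goes from about 84% to about 82% if both devices are truly at 15%, and to about 76% if the other device fails. With 158 evaluable the corresponding Holm figures are about 76% and 70%, below the stated 80%. Holding 80% when the other device fails would need about 201 evaluable per arm, or 201/0.9, so 224 enrolled with 10% drop-out.

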### Patient Enrollment, Inclusion/Exclusion Criteria

For potential enrollment in the RAPHE trial subjects must have a clinical indication for a radial approach coronary angiography and be between ages of 18 and 85 years. The use of standard 5, 6, or 7 French introducer sheaths will be required during the trial. A pre-screening sonographic evaluation of the radial artery will also be required to measure the diameter of the vessel. A minimum diameter of 1.8 mm-s is needed for potential enrollment. If a radial artery diameter of < 1.8 mm-s is detected, patients will discontinue the study as an early screen failure. Late screen-fail will occur if any other form of arterial puncture is needed during the procedure apart from the initial one, albeit upgrading the introducer size to a larger one will be allowed.

Exclusion criteria firstly focus on safety, thus potential patients shall be excluded based on the following: highly advanced age (>85 years) (I), sudden cardiac death and successful resuscitation prior to the index angiogram (II), unstable circulation prior to the index angiogram (III), pregnant or nursing (IV). Furthermore, three clinical exclusion criteria have been laid down, factors that are known to cause increased puncture site complications, to ensure no distortion of the collected data. These are: unusually small diameter of the radial artery (< 1.8 mm) (V), known and treated systemic autoimmune disease, e.g., rheumatoid arthritis, systemic lupus erythematosus etc. (VI) and severe, peripheral arterial vasculitis/disease, e.g., Buerger’s disease, Takayasu’s arteritis etc., (VII).

### Sample Size Calculation

Sample size calculation was carried out for non-inferiority studies following established guidelines (18, 19) with a significance level of 95% and a power of 80%. Although the best reported component of the DOCE, RAO rates range from < 1 to 33% (4), and it would be advisable to estimate sample size calculations for the worst-case scenario (i.e., 33%), however analyses of our own existing data regarding RAO and RAD (The RadPress trial—unpublished) deemed this value unreasonable for the centers involved. Therefore, we used a conservative 15% of the population rate for the DOCE for both intervention and control treatments. We allowed a 10% relative inferiority margin for the investigated treatments (20). The resulting sample size was 158 patients per arm. We also accounted for a potential 10% drop-out rate and factored in the uncertainty in true DOCE rates, and hence sample size estimates, and thus rounded the sample size to 200 patients per arm.

### Statistical Analyses

Data analysis will be done on an intention to treat basis. Baseline patient and disease characteristics will be summarized with detailed descriptive statistics that entail mean, median, SE, SD, IQR and range for continuous variables, while for categorical variables absolute and relative frequencies will be reported. Hypothesis testing of the primary outcome will be done with Fisher’s exact test with a significance level of 95%. Univariate analyses of secondary endpoints will be carried out as superiority analyses with one-way ANOVA, Kruskal-Wallis test, or logistic regressions, depending on the outcome variable type and distribution. Multivariate analyses of secondary endpoints will entail using general or generalized hierarchical mixed effects models depending on variable type and distribution. All statistical analyses will be done in the R statistical environment (21).

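### The primary hypothesis is non-inferiority, but the only primary test named is Fisher's exact test, which as stated has a null of equal proportions and is not tied to the margin

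*Protocol article*

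**What the plan says.** Three sections of the protocol article bear on this.

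- **Endpoint Definitions and Hypothesis.** The primary endpoint is the composite DOCE (bleeding with haematoma, radial artery damage, radial artery occlusion). The hypothesis is that "utilizing either of the novel bioactive devices in a standalone arrangement will prove clinically non-inferior to the other study and the control MCD, respectively". So there are two device-versus-control claims and one device-versus-device claim, all of non-inferiority.
- **Sample Size Calculation.** "Sample size calculation was carried out for non-inferiority studies", at a significance level given as 95% and 80% power. On the event rate: "we used a conservative 15% of the population rate for the DOCE for both intervention and control treatments". On the margin: "We allowed a 10% relative inferiority margin for the investigated treatments (20"). The result is 158 per arm, rounded up to 200 to cover 10% drop-out and uncertainty in the rate.
- **Statistical Analyses.** "Hypothesis testing of the primary outcome will be done with Fisher’s exact test with a significance level of 95" percent. No margin, shifted null, confidence bound or sidedness comes with it. The next sentence labels the secondary endpoints as superiority analyses; the primary endpoint gets no such label and no non-inferiority rule either.

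No other section carries the margin into the primary analysis.

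**The concern.** A non-inferiority claim requires the data to exclude a disadvantage as large as the margin. Fisher's exact test, as ordinarily defined, has equal proportions as its null. A significant result shows that the rates differ. A non-significant result does not say whether a difference as large as the margin has been excluded. The sample size was derived for one kind of test and the analysis section names another.

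What is at stake is the main conclusion. With truly similar devices, which is what the investigators expect, the named test will nearly always be non-significant, and the article gives no rule for moving from that result to the hypothesis. The obvious temptation would then be to treat non-significance as success, and that is easier to obtain when fewer patients are evaluable.

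**Working it through.** **Inputs.** DOCE 15% in both arms, 80% power, 158 per arm before inflation, 200 per arm final, 10% drop-out (all from Sample Size Calculation). Evaluable patients after drop-out: 200 × 0.90 = 180. Assumptions of this check: the 95% level means α = 0.05; Fisher's test is two-sided; sidedness of the non-inferiority test is not stated, so both one-sided 5% and 2.5% are shown.

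**Step 1: reproduce the stated sample size.** With equal rates p and margin d on the difference scale,

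n = (z₁₋α + z₀.₈₀)² × 2p(1−p) / d², where 2p(1−p) = 2 × 0.15 × 0.85 = 0.255.

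| Margin d | One-sided α | n per arm |
|---|---|---|
| 10 points | 5% | (1.645 + 0.842)² × 0.255 / 0.01 = 157.7, so **158** |
| 10 points | 2.5% | 201 |
| 1.5 points (10% of 15%) | 5% | 7,007 |
| 1.5 points | 2.5% | 8,896 |

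Of these, only 10 absolute points at one-sided 5% gives 158. The calculation therefore presupposes a margin-based test, on a margin that does not match its description as relative.

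**Step 2: what the named test does.** For n per arm and true rates p_C and p_T, the probability of significance is the sum of Bin(x_C; n, p_C) × Bin(x_T; n, p_T) over all pairs of counts with Fisher p < 0.05. For comparison, the margin-based rule passes when the Wald upper bound for the DOCE difference is below the margin.

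| True rates (control vs device) | n per arm | Fisher significant | Fisher non-significant | Margin-based pass, 10 points (5% / 2.5%) |
|---|---|---|---|---|
| 15% vs 15% | 200 | 3.6% (1.8% favouring the device) | 96.4% | 87.6% / 80.3% |
| 15% vs 15% | 180 | 3.5% (1.7% favouring the device) | 96.5% | 84.4% / 76.0% |
| 15% vs 25% | 200 | 66.5% | 33.5% | 5.1% / 2.6% |
| 15% vs 25% | 180 | 61.9% | 38.1% | 5.1% / 2.6% |
| 15% vs 25% | 158 | 55.3% | 44.7% | 5.2% / 2.6% |

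The mismatch does not depend on which margin is meant. With a device exactly 1.5 points worse (16.5% vs 15%, 200 per arm), Fisher is non-significant in 94.8% of trials; a test against a 1.5-point margin passes it in 5.1% (one-sided 5%) or 2.5% (one-sided 2.5%).

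**Step 3: two possible results at 200 per arm, control first.**

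- 30 vs 34 events: Fisher p = 0.68; difference 2.0 points, 95% CI −5.2 to 9.2. A 10-point margin is excluded.
- 30 vs 45 events: Fisher p = 0.072; difference 7.5 points, 95% CI −0.1 to 15.1. A 10-point margin is not excluded.

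Both are non-significant at 5%, yet they give opposite answers on non-inferiority.

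**Step 4: power of a margin-based test, by margin.** Power = Φ(d / √(0.255/n) − z₁₋α). For d = 0.10 and n = 200: √(0.255/200) = 0.0357 and 0.10/0.0357 = 2.80, so Φ(2.80 − 1.645) = 87.6% and Φ(2.80 − 1.960) = 80.0%. At n = 180 the values are 84.4% and 75.7%. For d = 0.015 and n = 200: 0.015/0.0357 = 0.42, giving 11.0% and 6.2%.

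**The case against.** The strongest defence is that the article condenses a fuller plan, which may contain a proper non-inferiority analysis. That would excuse silence, but the article is not silent: it names the primary test. A fuller plan with a margin-based test would contradict this sentence, so the sentence needs correcting either way.

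Several stronger readings are tempting and are not supported.

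- **That Fisher's test can never establish non-inferiority.** A significant result in favour of a device would imply it, although that happens in only about 1.8% of trials under the design assumption. Conditional exact methods can also be run against an odds ratio other than 1. The article states no such use and gives no odds-ratio margin, so the defensible statement is that the test as stated is not tied to the margin.
- **That the plan will count p > 0.05 as success.** No section says so. The 34% and 38% figures illustrate what that rule would do; they are not properties of a rule the plan adopts.
- **That the margin is 10 absolute points.** This is a back-calculation from 158. The text says relative. The figures at 25% vs 15%, and the 80% to 88% power, are conditional on the absolute reading.
- **That the test is a single omnibus comparison of three arms.** Nothing in the text says this, and which pairwise tables are tested may reasonably be left to the full plan.

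**Conclusion.** The point holds in this form: the stated primary test does not match the stated primary hypothesis or the stated basis for the sample size. This is a contradiction within the article and not a missing detail, and it holds whichever margin is intended, because the test as stated uses neither.

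On size, the test as written would support the hypothesis by significance in about 1.8% of trials under the design assumption, in a trial planned for 80% power. The pass rates of 34% (200 per arm) and 38% (180) for a device 10 points worse rest on two assumptions the article does not make: that non-significance is read as non-inferiority, and that 10 absolute points is a difference the trial should exclude. All figures assume a true control rate of 15% and a two-sided Fisher test at 5%.

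It should be corrected before analysis, since without it the article gives no workable test of its main claim.

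**What to change.** 1. **Reconcile the margin first** in Sample Size Calculation. State whether it is 10 absolute percentage points, which reproduces 158 at one-sided 5%, or 10% relative, which is 1.5 points on 15%. State the sidedness of the significance level at the same time.
2. **Replace the primary-test sentence** in Statistical Analyses along these lines: *For each bioactive device versus the control MCD, the difference in DOCE proportions will be estimated with a score-type confidence interval at the stated one-sided level; non-inferiority is declared if the upper bound lies below the pre-stated margin.* Any standard score-type interval will serve.
3. **Keep Fisher's exact test for superiority only.**
4. **State the same margin-based form for the device-versus-device hypothesis**, which Endpoint Definitions and Hypothesis also words as non-inferiority.

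The cost of items 2 to 4 is wording; no new data are needed. If 10 absolute points is confirmed, power is about 88% (one-sided 5%) or 80% (one-sided 2.5%) at 200 per arm, and about 84% or 76% at 180 evaluable. If the margin is 1.5 points, power at 200 per arm is only about 11% or 6%, and the planned size cannot support the non-inferiority claim; a change of wording in the analysis section would not cure that.

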The standalone potassium ferrate disc and chitosan sponge devices will both be used in a similar way. They will be placed onto the junction of the intact skin and introducer and manually compressed. To aid better initial compression and prevent device adhesion to bloody surgical gloves, a ball gauze will be placed on the chitosan device. The potassium-ferrate disc will be compressed alone. During compression the introducer will be removed, allowing for a visible amount of blood to appear, which will activate the hemostatic properties in both devices. Strong manual compression will be held for 1 min. Devices will then be banded and held in place using self-adherent wraps as detailed above. Strong, occlusive fixation of the devices will be upheld for a total of 10 min, after which the self-adherent bond will be fully unwrapped until the hemostasis device is visible. By this time both devices will have activated and initiated the coagulation cascade and are firmly attached to the puncture site. If acute bleeding occurs, an additional, minimum 5 minutes of compression will be applied. If initial devices are no longer fit for use, a new similar one will be used. Re-wrapping will then occur without the application of relevant pressure, in a non-occlusive way. During this time the wrapping will only protect the hemostasis device from external influence (e.g., accidental dislodgement, slipping etc.). If the second randomized study device also fails to contain puncture site bleeding a bail-out device of choice shall be applied as per protocol, the choice of which is left to the discretion of the attending physician. After a period of 120 ± 15 min the self-adherent wrapping will be removed. The chitosan sponge device will also be removed using sterile saline irrigation. The potassium-ferrate disc will remain in place and removed by the patient after 24 hours post-procedure.

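### For the two secondary time endpoints the hypothesis is each bioactive device shorter than the MCD, but the named tests (one-way ANOVA, Kruskal-Wallis) have no direction and no reference arm

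*Protocol article*

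**What the plan says.** **Hypothesis.** Endpoint Definitions and Hypothesis states that "the use of either one of the standalone bioactive devices will require less compression time, fewer human resources, and less management" than the MCD. The Discussion repeats the time part: patients in the two investigational arms "will achieve primary hemostasis quicker and require less overall compression time as compared to MCD control subjects". Both statements have a direction (less, quicker) and a comparator (the MCD).

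**Endpoints.** The secondary endpoints are time to primary hemostasis, overall device usage time, and number of devices used. Need for bail-out is listed separately as a tertiary endpoint. On units per patient and bail-out the Discussion says "We have no convincing assumptions regarding these endpoints".

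**Tests.** Statistical Analyses says that univariate analyses of the secondary endpoints will be "superiority analyses with one-way ANOVA, Kruskal-Wallis test, or logistic regressions", chosen by outcome type and distribution. The next sentence adds multivariate analyses with "general or generalized hierarchical mixed effects models depending on variable type and distribution". Neither sentence names a device-versus-MCD comparison for the time endpoints.

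**The concern.** One-way ANOVA and Kruskal-Wallis test a single null hypothesis: that the three arms do not differ. Rejection says that some difference exists. It does not say which arms differ or in which direction. The protocol's hypothesis is a pair of one-directional statements, chitosan shorter than MCD and ferrate shorter than MCD. The test labelled as the superiority analysis therefore answers another question.

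A significant result on a time endpoint could arise because both devices are shorter, only one is, both are longer, or only the two bioactive devices differ from each other. If it were reported under the superiority label, a device could be credited with a time saving that its own comparison with the MCD does not show. The time endpoints carry much of the trial's argument for saving staff effort, so the test and the hypothesis should match.

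**Working it through.** **Inputs**
- Three arms, 1:1:1, 200 per arm, 10% drop-out (Sample Size Calculation; Randomization Procedure). Evaluable: 200 × 0.90 = 180 per arm.
- Significance level 5%.
- Shifts of 0.3 and 0.4 SD, normal outcomes with common SD. These are assumptions. The article gives no effect size, SD or power for the secondary endpoints, so there is no figure of its own to reproduce here.

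**Step 1: the omnibus test cannot see direction.** ANOVA power depends on the noncentrality λ = n × Σ(μᵢ − μ̄)² / σ². In SD units, ordered MCD, device 1, device 2:
- Both shorter (0, −0.3, −0.3): μ̄ = −0.2, Σ = 0.04 + 0.01 + 0.01 = 0.06, λ = 180 × 0.06 = 10.8.
- Both longer (0, +0.3, +0.3): all signs flip, Σ = 0.06, λ = 10.8.
- One shorter, one equal (0, −0.3, 0): μ̄ = −0.1, Σ = 0.01 + 0.04 + 0.01 = 0.06, λ = 10.8.

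The critical value of F with 2 and 537 degrees of freedom is 3.01, and λ = 10.8 gives power 0.84 in all three cases. In simulation (4,000 trials per case) Kruskal-Wallis rejects in 83% when both are shorter and 83% when both are longer. At 200 per arm, λ = 12.0 and ANOVA power is 0.88 in every case.

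**Step 2: what signed contrasts say in the same cases.** Each contrast has noncentrality 0.3 / √(2/180) = 2.85 for a 0.3 SD shift. The two-sided Dunnett critical value for two contrasts is 2.212. The gated procedure is ANOVA at 5%, then each contrast at two-sided 5% (40,000 simulated trials).

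| True means (MCD, D1, D2), 180 per arm | ANOVA rejects | D1 / D2 shown shorter, Dunnett | D1 / D2 shown shorter, gated |
|---|---|---|---|
| 0, −0.3, −0.3 | 84% | 74% / 74% | 77% / 77% |
| 0, −0.3, 0 | 84% | 74% / 1.4% | 77% / 2.5% |
| 0, +0.3, +0.3 | 84% | 0% / 0% | 0% / 0% |
| 0, 0, +0.4 | 98% | 1.4% / 0% | about 2.5% / 0% |

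The first and third rows decide the point. The omnibus test rejects equally often when the hypothesis is true for both devices and when it is false for both; the contrasts separate the two.

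**Step 3: is the opposite direction conceivable?** Under Randomization Procedure the MCD starts at 12 ml and loses 2–3 ml every 10–15 min: 12/3 = 4 steps × 10 min = 40 min, up to 12/2 = 6 steps × 15 min = 90 min. This excludes time to primary hemostasis and any added air. The bioactive wrap stays for 120 ± 15 min, that is 105–135 min, and "The potassium-ferrate disc will remain in place and removed by the patient after 24 hours post-procedure". The direction for overall device time is therefore not assured. How large any reversal would be depends on which minutes the endpoint counts.

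**The case against.** **No rule for claims is stated.** A reader might infer that the plan would declare a device superior on an omnibus p-value alone. The article does not say so. It names tests, and the superiority label may only separate ordinary difference tests from the non-inferiority primary analysis. Follow-up contrasts are commonly left to an analysis plan, which is not shown, so their absence is not the point. What stands is that the article does name the superiority analysis for the time endpoints, and the named test does not address its hypothesis.

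**An omnibus test can be part of a valid procedure.** This stands. With exactly three arms, an ANOVA gate followed by pairwise contrasts at 5% controls the family-wise error, and Step 2 shows slightly more power per device than Dunnett. But that procedure is not in the article, and it also needs the signed contrasts.

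**Not every named method is omnibus.** This stands too. Logistic regression with the MCD as reference gives a signed odds ratio per device, and the mixed models can give signed arm effects, including for time.

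**Not every endpoint is directional.** For device count and bail-out the article offers no assumption, and bail-out is tertiary. A non-directional test does not conflict with anything stated about them, so extending the concern to them would be wrong.

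**The schedule does not prove a reversal.** A reader might conclude that overall time must be longer in the bioactive arms. After the first 10 min the wrap is non-occlusive, so wear time need not be compression time, and the Introduction cites 160 ± 43 min for MCDs alone. Group means or medians would also show the direction to a careful reader.

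**Conclusion.** The concern holds for the two secondary time endpoints when they are analysed by one-way ANOVA or Kruskal-Wallis. These tests do not test the stated hypothesis that each device takes less time than the MCD. Under assumed 0.3 SD shifts with 180 per arm, ANOVA rejects in about 84% of trials whether both devices are shorter or both are longer.

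The percentages rest on assumed effect sizes, normality and a common SD. The lack of direction does not: λ is unchanged when every shift changes sign. The weight is moderate, because the endpoints are secondary and the primary non-inferiority question is untouched. The documents do not support saying that all the named secondary analyses are wrong, or that the plan would credit a device from an omnibus result alone.

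**What to change.** In Statistical Analyses, define the superiority analysis of time to primary hemostasis and of overall device usage time as two signed contrasts, chitosan versus MCD and ferrate versus MCD. Give each an estimate and confidence interval: ANOVA contrasts, or Wilcoxon rank-sum with the Hodges-Lehmann shift if the distribution calls for it.

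Control error over the two contrasts by Dunnett or Holm, or keep the omnibus test as a gate followed by the signed contrasts. State that superiority is claimed only for a device whose own contrast favours it. State that the MCD is the reference arm in the logistic and mixed models.

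The cost is wording, with no new data or patients. Power per device for an assumed 0.3 SD effect at 180 per arm is about 74% with Dunnett or 77% with the gate, against 84% for the omnibus test, which answers a less specific question.
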